***2.2.1 Follow-up procedures***

**Main study**

The EVD survivors with at least one of the body fluid positive at RT-PCR will be asked to return for follow-up study visits, first time after two weeks then every two to four weeks until there have been two consecutive negative RT-PCR test results for each body fluid. Participants will be asked to continue follow-up until all body fluid specimens are negative for two consecutive visits.

Lactating women will receive their results within 3 days after the collection of the specimen. Women with positive results in breast-milk will be offered testing every 3 days till 2 consecutive tests are negative; women with a first negative test will come back after 3 days to do a confirmatory test.

Menstruating women will be asked to provide a specimen as close to the first day of their period as possible, and a second specimen before the end of the period. Menstrual blood sampling may be done at the same time as other body fluid testing, or may occur after testing of other body fluids has been completed.

Women will be offered pregnancy testing at every visit, and if positive they will be referred to ANC, pending on gestational age and needs, care will be offered in line with national guidelines for Ebola survivors. Pregnant women will be offered participation in the study.

Pregnant women will have an additional follow up questionnaire to record the outcome of delivery, which will occur if a pregnant woman delivers before she has completed the study follow up, or if the delivery takes place after body fluid testing has finished. A special questionnaire to record the pregnancy and delivery outcomes will be completed by the healthcare personnel providing ANC.

Breast-feeding women who test positive for EVD in breastmilk will be offered free formula feeding in line with current WHO guidelines.

A study card ID check will be done for each participant coming for a follow-up visit. If the participant has lost his/her study ID card, the locked in ID code may be accessed, if participant’s identity can be verified.

At each visit, participants will be informed of their RT-PCR Ebola test results (if available) including negative results. HIV testing will be offered at each visit. A follow-up questionnaire will be administered, including sexual behavior over the last two weeks since the previous visit, see Annex 1.

Participants will be asked to continue providing specimens of each body fluid and venous blood at every study visit until they have had two consecutive negative test results for that body fluid. Participants whose body fluids all have been RT-PCR negative at two consecutive study visits will exit from the study cohort.

For participants that have had two consecutive negative test results, a follow-up visit to administer a questionnaire and body fluid testing will be scheduled at 3 and 6 months after the last 2nd negative body fluid specimen has been collected. The same body fluids would be collected as in the initial visits, and the questionnaire will focus on health events and status since the last follow-up visit.

Interviews will take place in a designated private room at the study clinic.

A time to come back to the clinic for follow-up will be booked and agreed upon at each preceding visit. Contact information will be reviewed at each visit and reminder calls will be made if applicable. Study participants will be supported to fulfill their participation in the study by counseling offered at each visit together with assistance with referrals to clinical care as needed. Carefully timed reminder calls will be made to participants who have missed their appointments, and flexibility will be provided in terms of appointment bookings and any needs for additional counseling or information.

Renumeration for participation will be paid at each visit.

The participant will be offered test results from the preceding visits and offered counselling on transmission risks targeted to lab findings according to a standardized counseling script (Annex 2).

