**Project summary**

Little is known about the post-recovery persistence of Ebola virus (EBOV) and the risks of transmission from convalescent Ebola survivors during close or intimate contact. During this ongoing outbreak, it is important to fully understand how long the virus stays active in body fluids other than blood in order to reduce transmission and also which host factors determine persistence. Thus, we propose to investigate the persistence of the virus in different body fluids and its relation to immune response in a cohort of survivors, in order to target and refine public health interventions to arrest ongoing spread of disease. This will be an observational cohort study including survivors at different points of convalescence. Results and analyses will be used to update relevant counseling messages and recommendations from the Ministry of Health and Sanitation (MoHS), WHO, and US-CDC.

The study will be comprised of a pilot and a main study including specimens from adult men and women (serum, semen, vaginal secretions, and saliva, tears, sweat, urine, rectal swab, menstrual blood and breast milk if applicable), Participants will be recruited from Ebola treatment units (ETUs) and survivor registries and special efforts will be made to recruit HIV positive survivors. Participants in the study will be followed up at study sites in government hospitals.

Specimens will be tested for EBOV RNA by RT-PCR in Sierra Leone at 2-4 week intervals and the positive RT-PCR samples will be sent to US-CDC Atlanta for virus isolation. Each body fluid will be collected until two negative RT-PCR results at 2 weeks interval are obtained. Participants will be followed until all studied body fluids are negative. Analyses of antibody response, including titers of IgM and IgG, will be repeated in parallel to the body fluid tests.

Pilot and main study participants will be offered a follow-up visit with a questionnaire and body fluid testing at 3 and 6 months after their second negative RT-PCR test result.

Pregnant women will have an additional follow up to document the evolution of pregnancy, the outcomes of delivery, including products of delivery and body fluid testing. The process of this follow-up is detailed in the annex to this protocol

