**Pilot study**

Entry in the study will begin with informed consent followed by a standardized questionnaire and semen collection. All survivors with a positive RT-PCR will be asked to return for a follow-up visit including repeat semen collection, after two weeks. If the second semen specimen also is positive, follow-up with repeat semen collection will thereafter take place every two weeks until the RT-PCR has been negative twice. Thereafter study participation is discontinued. The follow-up appointments will follow the same clinic flow and testing algorithms. If the initial two tests are negative, participation is discontinued. The testing interval of two weeks may be extended to 4 weeks pending on preliminary results.

Laboratory results will be shared with the participant and transmission prevention counseling and condoms provided. HIV testing and counseling will also be provided in accordance with national guidelines.

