Titers of EBOV-specific IgG and IgM antibodies in blood will be analyzed by means of serology, at the field laboratory (Chinese-CDC in Jui). Blood for antibody analysis will be collected at the same time as body fluid specimens, and will hence be discontinued when the survivor has had two EBOV RT-PCR negative body fluid specimens from each fluid sampled.

At each visit, trained counselors will provide specific risk reduction counseling on the prevention of transmission of EBOV. Participants will be offered HIV testing and will receive counseling if they elect to be tested. All detected HIV positive patients will be referred to national HIV services if not already on antiretroviral treatment. A sufficient quantity of condoms will be offered at each visit. If needed, participants will be referred to clinical survivor services. Women will be offered pregnancy testing, and if positive they will be referred to ANC, pending on gestational age and needs, care will be offered in line with national guidelines for Ebola survivors. Pregnancy is not an exclusion criteria for this study.

Pilot and main study participants will be offered a follow-up visit with a questionnaire and body fluid testing at 3 and 6 months after their second negative RT-PCR test result. During the follow-up visits, a questionnaire asking about health events that occurred since their last study visit will be given, and body fluid specimens will be collected (for the pilot, semen specimens; for the main study, venous blood, semen or vaginal/menstrual blood as appropriate, rectal swab, sweat, urine, saliva, tears, and breast milk if applicable. If all body fluid specimens test negative, no further testing will be performed until the next scheduled 3 or 6 month visit. If a body fluid specimen tests positive, follow-up testing will be performed every 2 weeks until 2 consecutive negative specimens test results are obtained.

Pregnant women will be offered a special follow-up to monitor their pregnancy and delivery outcomes and the follow-up is detailed in Annex 3 “Ebola Viral Persistence study: Nested Pregnancy cohort study - VPNP”.

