**Flow charts for the main study (see below**): The first standardized interview will include demographics, sexual behaviors, and other information (refer to Annex 1). The collection of specimens will include venous blood, semen, vaginal secretions, rectal swabs, sweat, urine, saliva, tears, menstrual blood and breast milk as applicable. The participants will return after two weeks for a repeat specimen collection and a follow-up questionnaire, thereafter follow- up will take place every 2-4 weeks until all body fluids are confirmed negative twice by RT- PCR. Pending on preliminary findings in semen, the definition of a confirmed negative semen sample may be changed to comprise more tests.

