**3- and 6-Month Follow Up Visits Flowchart**

**
[figure not shown]
**

1. First study visit flowchart

[figure not shown]

* Women should return every 2 weeks to collect all body fluids, including vaginal swab, until 2 consecutive PCR negatives. Additionally, women should come to the site during regular hours when they begin menstruating to collect menstrual blood. They do need to notify the receptionist to schedule an appointment as close as possible to the first day of their period.

2. Follow up visit flowchart

[figure not shown]

*Women should return every 2 weeks to collect all body fluids, including vaginal swab, until 2 consecutive PCR negatives. Additionally, women should come to the site during regular hours when they begin menstruating to collect menstrual blood. They do need to notify the receptionist to schedule an appointment as close as possible to the first day of their period.

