**7. Data analysis plan**

• Descriptive analysis of the study participants will be performed by the study PI and staff with the support of WHO and US-CDC. WHO and US-CDC technical assistance may be provided as needed for these and any additional analyses of the study data. Any further statistical analysis will be conducted using adequate statistical program packages with the assistance of WHO and US-CDC.

• Viral Persistence time will be measured in days or months from time after symptom onset and will also be presented as time after ETU discharge.

• The primary measures of interest are:

o the period prevalence of viral persistence in 1st/baseline samples (0-3 months, >3-6 months etc)

o survival probabilities over time (based on base-line positive samples)

o maximum duration of tissue culture-positive results for EBOV by number of days since symptom onset for each of the various body fluid specimen types.

• EBOV presence, measured both as detected RNA and isolated virus, in any of the relevant body fluids, will be analyzed in relation to time of persistence.

• Analysis of RNA derived from selected specimens collected during the study will include genetic analysis and comparison with Ebola virus sequences derived from the participant. This will include sequences characterized during the acute phase of EVD (if available) and comparison with other Ebola virus sequences that have already been characterized. This will help to better describe the variation in virus sequence over time within individuals.

• Viral persistence in a body fluid at a certain period in time, will be analyzed in relation to host factors such as age, sex, co-morbidity including HIV and its clinical characteristics, severity of the earlier Ebola infection and Ebola sequelae, as well as presence and titers of IgM and IgG antibodies in serum. Information on exposure to experimental treatment or vaccination will also be taken into account in the analysis.

• Participant information on sexual history will be analyzed for frequency and type of

(protected/unprotected/vaginal/oral/anal) sex.

• The calculation of correlation between positive RT-PCR and culture tests for each body fluid specimen types will be performed, conditioned upon time since the first convalescent negative RT-PCR blood test.

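### The re-sampling interval is stated inconsistently, and Section 7 gives no clearance date or interval-censored method, so estimated persistence can depend on visit spacing

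*Combined protocol and SAP*

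**What the plan says.** **Schedule.** For the main study, Section 2.2.1 asks anyone with a positive fluid to return "first time after two weeks then every two to four weeks until there have been two consecutive negative RT-PCR test results for each body fluid". The flow-chart paragraph in Section 2 agrees: after a first return at two weeks, follow-up "will take place every 2-4 weeks until all body fluids are confirmed negative twice by" RT-PCR.

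The note printed under both the first-visit and the follow-up flow chart reads: "Women should return every 2 weeks to collect all body fluids, including vaginal swab, until 2 consecutive PCR negatives".

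The Project summary contains two rules: "Specimens will be tested for EBOV RNA by RT-PCR in Sierra Leone at 2-4 week intervals" and "Each body fluid will be collected until two negative RT-PCR results at 2 weeks interval are obtained".

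Other intervals also appear:
- After a late positive at the 3- or 6-month visit, Section 2 says "follow-up testing will be performed every 2 weeks until 2 consecutive negative specimens test results are obtained".
- Breast milk is tested every 3 days (Section 2.2.1).
- In the pilot, "The testing interval of two weeks may be extended to 4 weeks pending on preliminary results", and Section 2.1.2 allows pilot men to be merged into the main cohort.

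Nothing visible says when 2 weeks rather than 4 applies in the main study.

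**Analysis.** Section 7 lists among its primary measures "survival probabilities over time (based on base-line positive samples") and the longest culture-positive time since symptom onset. It does not say which date counts as clearance, and it names no estimator. Section 1.2.4 follows baseline positives until negativity is confirmed. Section 2.2.2 defines a negative as two negative RT-PCR results at consecutive visits, and allows that number to be amended.

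**The concern.** Nobody observes the day of clearance. The data show a last positive visit and a first negative visit, and clearance lies between them. If the analysis uses a visit date as the event time, every participant's time carries an error whose size is set by the spacing of visits. Spacing may run from 2 to 4 weeks, is 3 days for breast milk, and may have changed during the pilot.

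Survival probabilities for different fluids, for pilot and main participants, or for any groups seen at different intervals would then differ partly because of the calendar. The wording on confirmed negatives makes the second negative a natural choice of event date, and that choice carries the largest error. These estimates are meant to inform counselling and public recommendations on how long precautions are needed.

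**Working it through.** The plan states no figure that depends on the visit interval, so there is nothing of its own to reproduce. The question is how far each candidate clearance date lies from true clearance.

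**Inputs**
- First return at day 14, then every *g* days with *g* between 14 and 28 (Sections 2 and 2.2.1).
- Mean time *m* from the baseline positive to clearance. The documents give none, so I assume an exponential distribution with *m* = 30, 60 or 120 days.
- One clearance event per participant and no false negatives (assumptions).

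**Step 1, rule of thumb.** If clearance is spread evenly between visits, the first negative is late by *g*/2, the second by 1.5*g*, and the last positive is early by *g*/2. For *g* = 14 that gives +7, +21 and -7 days. For *g* = 28 it gives +14, +42 and -14 days.

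**Step 2, with the fixed first return.** Let p = exp(-14/m). The mean errors are:
- first negative: 14 + p × g / (1 - exp(-g/m)) - m
- second negative: the above + g
- last positive: the first-negative error minus the mean interval length, 14(1 - p) + g × p

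Example, m = 30 and g = 28: p = 0.6271 and 28 / (1 - 0.3932) = 46.15. The first-negative error is 14 + 0.6271 × 46.15 - 30 = 12.94. The second-negative error is 12.94 + 28 = 40.94. The mean interval length is 5.22 + 17.56 = 22.78, so the last-positive error is 12.94 - 22.78 = -9.84.

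A simulation of 400,000 draws per setting gave these mean errors in days:

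| m | g | Last positive | First negative | Second negative | Midpoint of last positive and first negative |
|---|---|---|---|---|---|
| 30 | 14 | -6.5 | +7.5 | +21.5 | +0.5 |
| 30 | 21 | -8.2 | +10.1 | +31.1 | +1.0 |
| 30 | 28 | -9.8 | +12.9 | +40.9 | +1.6 |
| 60 | 14 | -6.7 | +7.3 | +21.3 | +0.3 |
| 60 | 21 | -9.2 | +10.3 | +31.3 | +0.5 |
| 60 | 28 | -11.6 | +13.5 | +41.5 | +0.9 |
| 120 | 14 | -6.9 | +7.1 | +21.1 | +0.1 |
| 120 | 21 | -9.8 | +10.4 | +31.4 | +0.3 |
| 120 | 28 | -12.7 | +13.7 | +41.7 | +0.5 |

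**Step 3, contrast between two groups seen every 28 and every 14 days.**
- First negative: 12.9 - 7.5 = 5.4 up to 13.7 - 7.1 = 6.6 days.
- Second negative: 40.9 - 21.5 = 19.4 up to 41.7 - 21.1 = 20.6 days.
- Last positive: 3.3 to 5.8 days in the opposite direction.
- Midpoint: 0.4 to 1.1 days.

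For 21 against 14 days, the contrast is about 3 days at the first negative and about 10 at the second. With equal spacing it is zero.

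**Step 4, effect of the conflicting text.** Suppose visits are 4-weekly but the confirming negative follows after 2 weeks, as one sentence of the Project summary has it. The second-negative error is then 12.9 + 14 = 26.9 to 13.7 + 14 = 27.7 days instead of 40.9 to 41.7. So the choice between the two rules moves a confirmation-dated estimate by 14 days. Each further negative added to the definition adds another interval.

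**Step 5, measures affected.** Maximum duration is defined by positive results, so only the last-positive column bears on it, and wider spacing shortens it. Baseline period prevalence, and the upper limits of 7.1% and 3.6% for zero positives in 50 and 100, use first samples only and do not depend on re-sampling.

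**The case against.** A reader might infer that the plan puts women on 2-week and men on 4-week visits, so that a comparison of persistence by sex is biased by design. The documents do not support that. Two weeks lies within 2-4 weeks. Two-week intervals also appear for both sexes in the Project summary's stopping rule, in the re-testing after a late positive, in item 9 of the admission procedure, and in the recall period of the follow-up questionnaire. The specimen projections give men and women the same three visits, 2 × 2,520 = 5,040 specimens in the first 6 weeks. The flow charts themselves are not shown, so the men's boxes cannot be read. The Section 7 item on sex and other host factors concerns presence of virus in a period, not clearance time, and survival is not planned by sex. For fluids other than semen, the sample-size section expects prevalence near zero, so few baseline positives would be available to compare. All of this stands.

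It is also fair to say that the plan nowhere states that a visit date will serve as the clearance date. It is silent. Specimens are labelled with their date, so a sound analysis remains possible later. Against semen detections at 82, 140 and 199 days and at 9 months (Section 1.1), an error of one week is modest.

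None of this answers two points. The interval statements do not agree, and a primary measure lacks an event definition and an estimator while visit spacing may vary twofold.

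**Conclusion.** The point holds in two parts. First, the main-study interval is given in ways that do not match, and the passages must be reconciled. Second, Section 7 leaves survival probabilities open to an error set by visit spacing. At 14-day visits the mean error is about 7 days at the first negative and 21 at the second. At 28-day visits it is about 13 to 14 and 41 to 42. Dating at the last positive errs the other way, by about 7 and by 10 to 13 days.

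These sizes rest on an assumed exponential clearance time with mean 30 to 120 days, a first return at 2 weeks, one clearance event and perfect tests. The largest values also require visits that really are 4-weekly and dating at the confirming negative. A shift between sexes is possible but not prescribed, and is zero if both are seen equally often. The effect is likeliest to matter for semen, including merged pilot data. This should be corrected, but it does not undermine the baseline results.

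**What to change.** 1. Reconcile the interval statements in the Project summary, Section 2 (pilot and main study), the flow-chart notes and Section 2.2.1. State when each interval applies. This review does not choose one.
2. In Section 7, define time to clearance as interval-censored between the last positive and the first of the two consecutive negatives, using actual collection dates. Estimate it with the Turnbull estimator or a parametric interval-censored model. The estimate remains conditional on a positive baseline sample, as Section 7 already frames it.
3. State how a positive after two negatives is handled, since the plan expects that intermittent shedding may occur and tests for it at 3 and 6 months.
4. Report maximum culture-positive duration as the last positive day together with the date of the next specimen that tested negative.

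**Cost.** Protocol and analysis-plan wording, standard software and a little more analysis work. Confidence intervals will be slightly wider. No new visits, specimens or participants are needed.

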***2.2.2 Criteria for discontinuation of a participant***

1. The prospective data collection from a participant including specimen collection in the Main study will be discontinued when specimens from all relevant body fluids are negative (two negative RT-PCR test results at consecutive study visits constitute a negative, or else amended as per preliminary results.)
2. If the specimens test negative at the 3 and 6 month follow-up visits, no further visits will occur.
3. If male participants are unable to provide a semen specimen at 2 consecutive visits, they will be referred to specialized urological care via a survivor clinic. Additional eligible survivors may be recruited to replace these participants.

